## Abstract

**Background:**

Adult day programs provide critical supports to older adults and their family or friend caregivers. High-quality care in the community for as long as possible and minimizing facility-based continuing care are key priorities of older adults, their caregivers, and health care systems. While most older adults in need of care live in the community, about 10% of newly admitted care home residents have relatively low care needs that could be met in the community with the right supports. However, research on the effects of day programs is inconsistent. The methodological quality of studies is poor, and we especially lack robust, longitudinal research.

**Objective:**

Our research objectives are to (1) compare patterns of day program use (including nonuse) by province (Alberta, British Columbia, and Manitoba) and time; (2) compare characteristics of older adults by day program use pattern (including nonuse), province, and time; and (3) assess effects of day programs on attendees, compared with a propensity score–matched cohort of older nonattendees in the community.

**Methods:**

In this population-based retrospective cohort study, we will use clinical and health administrative data of older adults (65+ years of age) who received publicly funded continuing care in the community in the Canadian provinces of Alberta, British Columbia, and Manitoba between January 1, 2012, and December 31, 2024. We will compare patterns of day program use between provinces and assess changes over time. We will then compare characteristics of older adults (eg, age, sex, physical or cognitive disability, area-based deprivation indices, and caregiver availability or distress) by pattern of day program use or nonuse, province, and time. Finally, we will create a propensity score–matched comparison group of older adults in the community, who have not attended a day program. Using time-to-event models and general estimating equations, we will assess whether day program attendees compared with nonattendees enter care homes later; use emergency, acute, or primary care less frequently; experience less cognitive and physical decline; and have better mental health.

**Results:**

This will be a 3-year study (July 1, 2024, to June 30, 2027). We received ethics approvals from the relevant ethics boards. Starting on July 1, 2024, we will work with the 3 provincial health systems on data access and linkage, and we expect data analyses to start in early 2025.

**Conclusions:**

This study will generate robust Canadian evidence on the question whether day programs have positive, negative, or no effects on various older adult and caregiver outcomes. This will be a prerequisite to improving the quality of care provided to older adults in day programs, ultimately improving the quality of life of older adults and their caregivers.

**Trial Registration:**

ClinicalTrials.gov NCT06440447; https://clinicaltrials.gov/study/NCT06440447

**International Registered Report Identifier (IRRID):**

PRR1-10.2196/60896

## Introduction

Across the globe, societies are struggling to meet the needs of an aging population [1-5]. The increasing prevalence of dementia [6-8] and comorbid chronic conditions [9,10] lead to complex care needs [9,10] and to greater family or friend caregiver burden [11-14] (ie, “the extent to which caregivers perceive that caregiving has had an adverse effect on their emotional, social, financial, physical, and spiritual functioning” [15]). In response, health systems provide a range of ongoing care and supports to older adults and their caregivers—in Canada commonly referred to as continuing care [2,16]. Continuing care can be provided in an older adult’s private home, in the community (eg, an adult day program), or in a variety of congregate care settings including independent living, retirement homes, supportive or assisted living, or nursing homes (NHs) [17,18]. Governments have identified NHs as a major driver of public continuing care costs [17,19-21]. To mitigate pressures on public continuing care systems, and to meet aging in place preferences of older adults and their caregivers [22-24], reforms have implemented aging in place strategies. These strategies largely include (1) reserving NH care to those with the most complex care needs, and (2) improving access to an array of publicly funded continuing care options in the community [2].

Adult day programming is such a continuing care option to support aging in place [25-32]. Older adults in need of continuing care usually attend these programs for parts of the day, returning to their homes overnight (but overnight services are provided by some day programs). As this literature illustrates [25-32], the number of days a person attends a day program can vary widely, depending on the program and health jurisdiction, from a couple of days or month to daily attendance. The amount of time an individual attends also varies from a few hours or day to all day, or sometimes during nights, and so do admission criteria, supports and services offered, and funding models.

Despite these variations, day programs have unique characteristics that set them apart from other continuing care options. Day programs employ care staff and admit people with a certain level of support needs [30,33]. This distinguishes them from senior or community centers [34] and creative arts programs [35], which are open to independent older adults, do not employ care staff, and are organized more informally. Unlike home care [36] or in-home respite [37], day programs serve groups of older adults in a setting external to the attendee’s home [30,33], supporting social interactions and caregiver respite [32]. Unlike geriatric day hospitals, which provide medical, therapeutic, and rehabilitative care for a few weeks [38], day programs prioritize social and recreational activities, and they do so for long term (often for months or years) [30,33]. Day program services and supports usually include transportation; meals; recreational activities (eg, playing games, musical activities, crafting, and painting); socializing with other clients and day program staff; physical, cognitive, and spiritual activities; social work counseling; and case management support. Personal, nursing, and medical care are often not provided, or only to a limited extent, depending on the program and health system.

Recent literature reviews [28-32,39] reveal a growing body of evidence that suggests that day program attendance may be associated with attendees’ improved mental health, cognition, loneliness, quality of life, perceived health, physical functioning, use of polypharmacy, and mortality. These reviews also suggest that attendance may be associated with older adults’ delayed admissions to congregate care, reduced risk for hospitalization, improved caregiver burden, and caregivers’ feelings of competence, mental health, and well-being. However, reviews point to inconsistent findings, methodological limitations, and substantial heterogeneity of included studies. For example, a Canadian 1-group pre-post study suggested that Geriatric Depression Scale scores decreased (fewer depressive symptoms) from 5.0 at admission to a day program to 3.3 at discharge (*P*=.007). A quasi-experimental study comparing depressive symptoms between day program attendees with dementia and nonattendees with dementia in the United States [40] found no group differences. However, on days of attendance, the proportion of caregivers who reported depressive symptoms for attendees decreased over time (from 32/133, 24% to 25/133, 19%; *P*<.02). A Canadian randomized controlled trial [41] found no difference in depressive symptoms between day program attendees and wait-listed nonattendees.

Across the literature, four key knowledge gaps persist: (1) we generally know little about the characteristics of day program attendees and nonattendees, or about those with different patterns of use. (2) We lack longitudinal data on changes in the aforementioned outcomes. (3) Generally, the methodological quality of available studies is poor [32], and we lack robust, large-scale, longitudinal evidence of older adult day programs on day program attendees—especially those living with dementia. With few notable exceptions [42,43], we especially lack current research on Canadian day programs with most research originating from the US or Canadian studies often dating back several decades [25,26,44]. (4) Differential effects of day programs on persons with multiple, intersecting vulnerabilities are poorly understood, despite inequity concerns [39,45-47]. Advanced age puts individuals at risk of ageism; physical and cognitive disabilities may expose them to ableism; the majority of older adults and their caregivers are women, often experiencing gender inequities; and giving and receiving care are associated with substantial health care costs, disproportionally affecting those with low income [48]. Racism or transphobia or homophobia can further increase these pressures, severely affecting older adults and their caregivers [49,50].

Our study will address these knowledge gaps comprehensively, rigorously, and simultaneously. We will address the following 3 research objectives:

Explore patterns of day program use (eg, variations in time to first attendance, monthly hours of attendance, ongoing versus interrupted attendance, and total time of day program exposure), using latent class analyses (LCA), and compare the frequency of each latent use class between provinces and over time.Compare older adults’ demographic, social, and health characteristics (eg, age, sex, physical or cognitive disability, area-based deprivation indices, and caregiver availability or distress) by day program use or nonuse class, province, and time.Assess whether, compared with a propensity score–matched control group of nonattendees, day program attendees enter care homes at later points in time; use emergency, acute, or primary care less frequently; experience less cognitive and physical decline; have better mental health; and have less distressed caregivers. We will assess potential modification of these effects by day program use or nonuse class, age, sex, and social determinants of health (eg, area-based deprivation indices).

## Methods

### Study Design

Using an integrated knowledge translation (iKT) approach [51,52], we partnered with a cross-Canadian team of experts to design this population-based retrospective cohort study (ClinicalTrials.gov; NCT06440447) covering the Canadian provinces of Alberta, British Columbia, and Manitoba, and we will collaborate with our experts throughout the study. Experts include older adults (some with dementia), their caregivers, Alzheimer societies, caregiver organizations, day program staff and managers, and government and health system decision makers. They will provide intimate knowledge of day programs, and the experience of attending them or caring for an attendee, which will help us interpret and contextualize our findings. We will use deidentified clinical and health administrative data from each of the 3 provinces. Our study will follow the STROBE (Strengthening the Reporting of Observational Studies in Epidemiology) [53], and the REporting of studies Conducted using Observational Routinely-collected health Data (RECORD) [54] guidelines. Provincial data policies require data to remain in each respective province, preventing linkage across provinces and analyses of all data in one place. Therefore, in-house data analysts with each provincial health system will carry out the analyses separately with shared protocols and programs.

### Setting and Sample

Our study settings are community-based continuing care systems. Each province provides access to a range of publicly funded community-based continuing care services, including adult day programs [55-63]. Each provincial health system determines and enacts access criteria and provides services (directly or via contracted providers) [55-63]. Day program eligibility is assessed in each province, using comparable processes, criteria, and assessments (ie, the Resident Assessment Instrument—Home Care [RAI-HC], a standardized, valid, reliable assessment tool [64]) [60,65,66]. To be eligible, attendees need to have not only some care dependency but also the ability to cope to some extent with activities of daily living, ambulate or transfer with no or minimal assistance, be continent or independent in managing continence products, exhibit no or easily manageable responsive behaviors, and either be alone for extended periods or have a caregiver who requires respite. Our study cohort will include all individuals aged 65 years or older with an initial RAI-HC assessment completed between January 1, 2012, and December 31, 2021. We will follow everyone until they move into a care home, are lost to follow-up (eg, because of death, moving out of province, loss of public insurance eligibility), or until December 31, 2024 (the end of the period covered by our data). That will allow for a care trajectory of at least 3 years (for those with an initial RAI-HC assessment in December 2021), enabling us to assess the number and characteristics of individuals with different day program use patterns, and compare them with those who were never exposed to a day program.

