#### Study Outcomes

The data sources noted above enable us to examine a range of important study outcomes. Data on the time between a person’s first RAI-HC assessment and admission to a care home will come from provincial continuing care registries. Symptoms of depression will be assessed using the validated RAI-HC Depression Rating Scale [72], with scores ranging from 0 to 14 and a cut point of 3 or higher representing clinically meaningful depressive symptoms [72,73]. We will capture physical and cognitive decline, using validated RAI-HC scales [64]: the Activities of Daily Living Hierarchy (ADLh) Scale [74] and the Cognitive Performance Scale (CPS) [75]. Both scales range from 0 (no impairment) to 6 (maximum impairment), and our outcomes will be dichotomous, indicating any increase (vs no change or a decrease) between the previous and follow-up measurement in each of these scales. Using care practitioner claims data, we will generate rates of different types of primary and specialist care use (eg, family physician, specialists, nursing practitioner, and allied health providers). We will use the DAD and NACRS databases to generate rates of emergency department registrations, hospital admissions, and days in hospital (including alternative level of care) [43]. Rates will be stratified by day program use or nonuse pattern.

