#### Objective 3: Assess Effects of Day Programs

To create a propensity score, we will run a logistic regression for each province with day program attendance or nonattendance as the dependent variable and adding matching covariates. We will use one-to-one matching (1 matched nonattendee for every attendee) [78]. We will use matching without replacement [85] and apply an optimal caliper matching algorithm [86]. As per best practice recommendations [87], we will use a caliper width of 0.2 of the SD of the propensity score’s logit. If this matching approach does not allow us to achieve a sufficient sample size, we will use propensity score quintiles for matching.

We will compare sample characteristics and study outcomes between attendees and nonattendees in every year and province, using bivariate statistical tests (eg, chi-square test or Fisher exact test for categorical variables, *t* tests, or ANOVAs for continuous variables, and their nonparametric equivalents if variables violate statistical assumptions). To assess the effect of day program exposure on time to care home admission, we will specify a multilevel time-to-event model with a health region–level random effect [88]. Health systems in each of the 3 provinces are divided into 5 health regions [89-91], and regional policies may cause clustering effects that our models must account for. Each model will include day program use or nonuse class as independent variable and will be adjusted for time-varying variables. These will include matching variables, if appropriate (ie, in case of group differences in matching variables over time or due to missing data) [80-82] and, if needed, additional covariates (eg, demographics, social determinants, medical or functional conditions, and non–day program community care). Covariates that differ between attendees and nonattendees with a *P* value of ≤.15 in the bivariate analyses will be considered for inclusion. We will add covariates stepwise, one-by-one, and remove those that cause collinearity issues or decrease model fit. As in objective 2, we will pool provincial effects statistically, using random-effects mixed regression models.

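### Death precludes care home admission but is classed as loss to follow-up, so the admission hazard ratio alone cannot show whether attendees actually enter care homes later or less often

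*Protocol article*

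**What the plan says.** All places are in the protocol article.

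- **Setting and Sample** defines the cohort as "all individuals aged 65 years or older with an initial RAI-HC assessment" in 2012 to 2021. Besides care home entry, follow-up ends when people "are lost to follow-up (eg, because of death, moving out of province, loss of public insurance eligibility"). Everyone still under observation at the close of 2024 stops there, when the data run out. The section adds: "That will allow for a care trajectory of at least 3 years". People assessed at the start of 2012 can have up to 13 years.
- **Study Outcomes** takes the outcome as the time between a person's "first RAI-HC assessment and admission to a care home". Mortality is not among the outcomes.
- **Introduction** (third objective) asks whether "day program attendees enter care homes at later points in time" than matched nonattendees. The same section's literature summary ends its list of attendee outcomes possibly associated with attendance with "use of polypharmacy, and mortality".
- **Objective 3** states: "To assess the effect of day program exposure on time to care home admission, we will specify a multilevel time-to-event model". The model carries a random effect for health region. **Sample Size Calculation** uses a Cox model and an HR of 0.6 for admission.

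No section mentions a competing event, cumulative incidence, or a combined admission-or-death outcome.

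**The concern.** Someone who moves out of province can still enter a care home unobserved. Someone who dies cannot. The first is missing information; the second is an outcome in its own right. Listing death as the first example of loss to follow-up treats the two alike.

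This matters here for two reasons. The cohort is aged 65 or older, has care needs and is followed for 3 to 13 years, so deaths should be common. And the article itself allows that attendance may be related to mortality, so the competing event may differ by exposure group.

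At stake is how the main result will be read. The Discussion presents the study as telling health systems whether day programs delay care home admission. That question concerns real time in the community and real admissions. Both depend on the death rate in each group as well as on the admission hazard.

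**Working it through.** **The plan's own figure.** Schoenfeld's formula for HR 0.6, 1:1 groups, power 0.80 and alpha 0.05 (two-sided assumed) gives 120.3 events. Dividing by 1 − 0.25 for the covariates gives 160.4. The stated total of 1327 then implies an event probability of about 160.4 / 1327 = 0.121, which the article does not state. The figure is not shown to be wrong, and nothing below depends on it.

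**Inputs.** The article gives no admission or death rates. All rates below are assumptions, constant over time: admission hazard *a* and death hazard *d* per year.

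- Actual share admitted by time *t* (cumulative incidence): a/(a+d) × [1 − exp(−(a+d)t)]
- Share admitted as read from a death-censored curve: 1 − exp(−a·t)
- Mean time alive in the community up to *t*: [1 − exp(−(a+d)t)]/(a+d)

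**Step 1: a mortality effect with no effect on the admission hazard.** Take a = 0.12 in both groups, so the cause-specific admission HR is 1.0. Let d = 0.15 in nonattendees and 0.8 × 0.15 = 0.12 in attendees, with t = 10.

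- Nonattendees: 0.12/0.27 × (1 − exp(−2.7)) = 0.444 × 0.933 = 41%
- Attendees: 0.12/0.24 × (1 − exp(−2.4)) = 0.500 × 0.909 = 45%
- Mean time alive in the community: 0.933/0.27 = 3.45 years against 0.909/0.24 = 3.79 years

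More attendees are admitted because more live long enough, and they also spend longer at home. The HR of 1.0 shows neither.

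In the other direction, take a death HR of 1.5 (d = 0.225 against 0.15) with a = 0.12 and t = 5. Admissions fall from 0.444 × (1 − exp(−1.35)) = 33% to 0.348 × (1 − exp(−1.725)) = 29%, again with an HR of 1.0.

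**Step 2: is the HR itself biased?** Cox models with deaths censored were fitted to 1,000,000 simulated people per scenario. The true admission HR was 1, the admission hazard 0.10, the death hazard 0.10 or 0.20, and follow-up 5 years.

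| Unmeasured frailty shared by death and admission | Death HR 0.6 | Death HR 0.8 | Death HR 1.5 |
|---|---|---|---|
| None | 1.00 | 1.00 | 1.00 |
| Gamma, variance 0.5 to 2 | 1.04 to 1.14 | 1.02 to 1.06 | 0.96 to 0.88 |

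Without shared frailty the estimates lay between 0.997 and 1.003. With it, lower mortality in attendees pushes the HR above 1 and can hide a benefit. Higher mortality pushes it below 1 and can imitate one.

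**Step 3: absolute risk, if one were read from death-censored curves.**

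| t (years) | a | d | Death-censored | Actual | Gap (points) |
|---|---|---|---|---|---|
| 5 | 0.10 | 0.12 | 39.3% | 30.3% | 9.0 |
| 5 | 0.10 | 0.18 | 39.3% | 26.9% | 12.4 |
| 5 | 0.15 | 0.12 | 52.8% | 41.2% | 11.6 |
| 5 | 0.15 | 0.18 | 52.8% | 36.7% | 16.0 |
| 8 | 0.10 | 0.12 | 55.1% | 37.6% | 17.4 |
| 8 | 0.15 | 0.18 | 69.9% | 42.2% | 27.7 |

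The 8-year rows are the smallest and largest gaps over the same grid.

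**The case against.** The strongest reply is that follow-up must end at death under any method, so Setting and Sample may only say when observation stops. The article never says that deaths are censored, a time-to-event model can be a competing-risks model, and a condensed article can leave event coding to a fuller plan. It is true that censoring is inferred and not stated. But the article does more than stay silent: it names death as a form of loss to follow-up, and a fuller plan would have to override that wording.

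Two stronger readings are tempting, and the documents support neither.

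- A reader might infer that a mortality effect will pass into the admission HR. Step 2 shows that this is not a general property of censoring deaths. If death and admission are independent given the covariates, the HR is unaffected. It is a recognised estimand for the effect on the admission rate. Bias needs residual shared frailty. The assessment data cover function, cognition and diagnoses, which limits it. The Limitations section says that some important variables are unavailable, so it cannot be excluded.
- A reader might infer that the study will report overstated admission risks. The article commits to no absolute risk and no Kaplan-Meier curve, so Step 3 is a conditional warning.

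Leaving mortality out of the outcome list is in itself a choice the authors may make. The difficulty is that time to admission cannot be interpreted without deaths by group.

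**Conclusion.** The point holds as one of classification and interpretation. Death is placed with loss to follow-up for an outcome that it precludes, and no competing-event handling is named. The planned HR is valid as a cause-specific HR, but does not by itself answer whether attendees enter care homes later or less often.

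Under the assumed rates, a 20% lower death hazard moves 10-year admissions by 4 points (41% to 45%) at an HR of exactly 1.0. With shared frailty of the assumed strength, a null HR moves to between 0.88 and 1.14, in a direction set by the mortality difference. Death-censored absolute risks, if anyone reports them, would be 9 to 16 points too high at 5 years and 17 to 28 points at 8 years.

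These sizes rest on assumed constant hazards, because the documents give no rates. That death and loss of information are different events does not rest on them. The change should be made before the programs shared by the three provinces are fixed.

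**What to change.** - **Setting and Sample:** list death separately from loss to follow-up and define it as a competing event for care home admission. Keep censoring for moves out of province, loss of insurance eligibility and the end of data.
- **Objective 3:** keep the cause-specific HR for admission, and report the cause-specific HR for death beside it from a model of the same form. Add Aalen-Johansen cumulative incidence of admission and of death by group. The difference in restricted mean time alive in the community is an optional addition that speaks directly to the aim of staying at home longer.

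The cost is a wording change and two extra standard outputs per province. No new data are needed, since death already ends follow-up and must be recorded.
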